### Treatment Assignment

Radiation therapy according to the protocol will be performed in patients included into the study and after assignment of the patients to the treatment arms after randomization.

Patients withdrawn from the trial retain their identification codes (e.g. randomization number, if already given). New patients must always be allotted a new identification code.

### Treatment Planning

For FSRT and particle therapy, patients will be immobilized using an individually manufactured head mask. For treatment planning, contrast-enhanced CT as well as MR-imaging will be performed for optimal target definition.

Treatment planning for carbon ion and FSRT is to be performed about 1-2 weeks prior to the start of re-irradiation.

Organs at risk such as the brain stem, optic nerves, chiasm and spinal chord will be contoured. Dose constraints of normal tissue will be respected according to Emami et al. [16].

The Treatment Volume for Re-Irradiation will be defined as the area of contrast enhancement on T1-weighted MR-imaging adding a safety margin of 5 mm.

Amino-Acid-PET or SPECT-Examinations may be used in addition to contrast-enhanced MRI for target volume definition but are not mandatory.

FSRT planning is performed using standard photon-treatment planning systems such as HELAX, Masterplan or STP.

Carbon ion RT planning is performed using the treatment planning software PT-Planning (Siemens, Erlangen, Germany) including biologic plan optimization. Biologically effective dose distributions will be calculated using the a/β ratio for gliomas as well as for the endpoint late toxicity to the brain.

No interruptions > 4 days during study treatment (carbon ion radiotherapy or FSRT) are allowed.

Patient positioning prior to FSRT or particle therapy will be evaluated by comparison of x-rays to the DRRs. Set up deviations >3 mm are corrected prior to radiotherapy.

### Dose Prescription Experimental (Carbon) Arm

The intensity-controlled rasterscan system will be used for beam application. In the Phase I Dose Escalation Part, increasing doses of carbon ion radiotherapy will be evaluated in 7 steps starting at 10 × 3 Gy E up to 16 × 3 Gy E. In this part, the RD of carbon ion radiotherapy for re-irradiation of gliomas will be determined.

Therafter, the RD determined will be chosen for the randomized phase II part of the study. The total dose will be prescribed to the maximum of the calculated dose distribution for the target volume. Treatment planning aims in the coverage of the target volume by the 90%-isodose line.

Dose specification is based on biologic equivalent dose because of the high RBE of carbon ions, which differs throughout the target volume due to its dependence on various factors. RBE will be calculated at each voxel throughout the target volumes and biological optimization will be performed. The dose prescription used is related to the isoeffective dose GyE using daily fractions of 2 Gy and a weekly fractionation of 5 × 3 Gy.

A typical treatment plan is shown in Fig. 2.

**Figure 2 F2:**
[figure not shown]
**Typical treatment plan for carbon ion radiotherapy for a patients with a recurrent glioblatoma**. Treatment is performed using the Siemens TPS for particle therapy, target volume delienation is based on CT- and MR-imaging with contrast enhancement.

### Dose Prescription Standard (Photon) Arm

Eighteen fractions of a single dose of 2 Gy up to a total dose of 36 Gy will be prescribed to the isocenter. Treatment planning aims in the coverage of the target volume by the 90%-isodose line.

### Statistical calculations for trial sample size

The statistical methods applied for this study are subject to GCP guidelines (Guidelines of the International Conference on Harmonisation (ICH) e.g.

• ICH E3: Structure and Contents of Clinical Study Reports,

• ICH E6: Good Clinical Practice (GCP). Consolidated Guideline,

• ICH E9: Note for Guidance on Statistical Principles in Clinical Trials) and will be performed in accordance with CESAR SOP 8 (Statistical Analysis/Biometry) in their versions valid at the date of the original study protocol.

### Study Hypothesis

#### Phase I

Phase I part of this study is conducted to choose the Recommended Dose (RD) of carbon ion radiotherapy for the phase II part between seven dose levels based on the dose escalation scheme.

#### Phase II

The phase II part of this study is designed to demonstrate superiority in survival of carbon ion radiotherapy (experimental) to FSRT (standard) in patients with recurrent or progressive gliomas. The primary endpoints variable is overall survival time after at least 12 months of follow-up (OS_12m) defined as time to death for any reason during the follow-up period of at least 12 months starting from date of randomization.

### Sample Size Calculation

#### Phase I

Seven DLs are included in the dose finding part. It is assumed that the probability of a DLT is 1/3. With n = 8 patients in each DL, the power that at each DL at least one DLT is observed is greater than 95%. Therefore a maximum of 56 patients will be treated in the phase I part of this study.

Within this study, DLTs are defined as any grade IV toxicity according to CTCAE Version 4.0 associated to study treatment.

#### Phase II

• The size of the phase II part of this study is determined by the primary aim of testing experimental treatment for superiority over standard treatment. This endpoint is a censored failure time.

• Information on the OS_B__12mR (overall survival rate after 12 months of follow-up for standard treatment) is given in literature data [17].

To calculate survival data, a population distribution of GBM in 34.3%, Grade III Tumors in 24.4% and low grade gliomas in 41.3% was used [17]. Survival rates for overall survival were taken as published previously with 23% for GBM 65% for Grade III, and 77% for low-grade gliomas observed at 12 months after re-irradiation [17].

Overall OS_B__12mR can be calculated as weighted mean rate. Therefore OS_B__12mR is expected to be 56%. The study will be designed to detect an improvement in OS_12mR of 10% (OS_A__12mR = 66%).

The statistical error rates for this test of superiority are set as α = 0.05 and β = 0.20 (power 80%). Sample size calculation is based on an unstratified log-rank. It can be expected that including histology in a stratified log-rank test will increase the power as compared to the unstratified test.

The recruitment period will be 36 months with a minimal follow-up time of 12 months. In order to put more patients on the experimental treatment, an unbalanced randomization allocation ratio of 2:3 was chosen.

For this set of assumptions, the sample size calculation programme PASS 2008 yields the total sample size for standard treatment of n = 138 and n = 207 for experimental treatment. Allowing for failures for various reasons of 10%, a total of N = 380 is required for this part of the study (n = 152 in standard arm and n = 228 in experimental arm). Patients will be stratified by histology.

### Statistical Methods

#### Phase I

##### Primary endpoint

Safety will be assessed by the type, incidence and severity (graded by the NCI CTC-AE Version 4.0) and relation to treatment. All patients treated at least once with one of the seven dose levels defined above will be described individually and summarized by dose level. No confirmatory statistical analysis will be performed.

### Secondary endpoint

Descriptive summary tables will be presented on baseline patient characteristics as well as for all safety parameters by dose level. Patients will be monitored for adverse events using NCI-CTC version 4.0.

#### Phase II

##### Primary endpoint

The primary endpoint variable OS_12 m was planned to be analysed by a one sided logrank test of stratified by histology testing H_0_: OS_A_-12 m = OS_B_-12 m versus H_1_: OS_A_-12 m > OS_B_-12 m at the level of alpha = 5%. One interim analysis is planned when 50% of the number of expected events under the null-hypothesis have occurred. In order to preserve the significance level of 5% a sequential plan with alpha-spending of De-Mets and Lan with limits of O'Brien and Fleming is applied.

Overall survival will be summarized by Kaplan-Meier curves. Median estimates as well as associated 95% confidence intervals will be reported. Further, a descriptive analysis of the primary outcome variable is performed applying a Cox-regression model.

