#### Phase II

For the primary aim and the primary endpoint of the phase II, one interim analysis will be performed when 40% of the expected events under the null-hypothesis have occurred. Under the study hypotheses, 114 events will be occurred under the null hypothesis approximately after 26 months after start of recruitment.

Using O'Brien-Fleming approach with one scheduled interim analysis, hypothesis testing would be conducted at an interim significance level of α = 0.008. If significance is found in favour of the test treatment, the study may be stopped with sufficient statistical evidence of efficacy. If the level of significance is not reached at the interim analysis, the study continues to normal completion at which time the hypothesis testing is conducted at a significance level of α = 0.042. This stagewise procedure will have an overall significance of α = 0.05.

If for any reason no confirmative interim analysis will be performed, the final significance level will be 5%.

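### The one phase II efficacy interim has two written triggers, 50% and 40% of expected null events, and the section giving 40% pairs it with a significance level that sits nearer a 50% look.

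*Protocol article*

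**What the plan says.** Two sections of the protocol article describe the single confirmatory interim analysis of phase II overall survival.

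- Statistical Methods, Phase II, Primary endpoint: "One interim analysis is planned when 50% of the number of expected events under the null-hypothesis have occurred". It names a Lan-DeMets alpha-spending plan with O'Brien-Fleming limits, for "a one sided logrank test of stratified by histology" at 5%.
- Interim Analysis, Phase II: "one interim analysis will be performed when 40% of the expected events under the null-hypothesis have occurred". It continues: "Under the study hypotheses, 114 events will be occurred under the null hypothesis approximately after 26 months after start of recruitment". It sets significance levels of 0.008 at the interim and 0.042 at the end, and allows the study to stop for efficacy at the interim.

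The design figures are in Sample Size Calculation, Phase II: 12-month survival of 56% versus 66%, 36 months of recruitment plus at least 12 months of follow-up, 2:3 allocation, and 345 patients (138 + 207) raised to 380 for failures. The article gives neither the total number of expected events nor the N on which 114 was counted.

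**The concern.** Both statements concern the same analysis, the same endpoint and the same null-hypothesis base, so one of the two fractions must be wrong. This is not detail left to the SAP: the article fixes the fraction twice, at different values.

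The fraction matters in two ways. It decides how many deaths trigger a look that may end the trial. Under a Lan-DeMets plan it also decides how much alpha is spent there. A reader would hope that the stated count, calendar time and significance levels show which fraction was meant, so these have to be checked against each other.

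**Working it through.** **Inputs.** From Sample Size Calculation, Phase II: 12-month survival 56% (standard) and 66% (experimental), 36 + 12 months, allocation 2:3, N = 345 or 380, power 80%. From Statistical Methods: one-sided alpha 0.05. Assumed: exponential survival, uniform accrual, no further losses.

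**1. Does this model reproduce the plan's sample size?**
- Hazards: −ln(0.56)/12 = 0.0483 and −ln(0.66)/12 = 0.0346 per month; hazard ratio 0.717.
- Events needed (Schoenfeld): (1.645 + 0.842)² / (0.4 × 0.6 × (ln 0.717)²) ≈ 232, rounded up to 233.
- Probability of death by month 48, P = 1 − (e^(−12λ) − e^(−48λ))/(36λ): 0.7346 on the standard hazard, 0.6228 on the experimental hazard. Weighted under the alternative: 0.4 × 0.7346 + 0.6 × 0.6228 = 0.6675.
- N ≈ 233/0.6675 = 349, within about 1% of the stated 345. The model is adequate, and the design is one-sided.

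**2. Null totals and the two triggers.**

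| N | Null total (N × 0.7346) | 40% | 50% | 114 as share |
|---|---|---|---|---|
| 345 | 253.4 | 101.4 | 126.7 | 45.0% |
| 380 | 279.1 | 111.7 | 139.6 | 40.8% |

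During recruitment, null deaths by month t are N × [t − (1 − e^(−λt))/λ]/36. For either N, the 40% point falls at 25.1 months and the 50% point at 28.8 months. At N = 380 the triggers are about 28 deaths and 3.6 months apart.

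**3. Which fraction do 114 events at about 26 months indicate?**
- At N = 380, 114 null deaths fall at 25.4 months; at N = 345, at 27.0 months.
- At month 26 the null information fraction is about 42%, whatever N is.
- The 40% reading at N = 380 therefore fits both the count and the time.
- A 50% reading can match the count: 114 is 49.5% of the 230.3 deaths expected under the alternative at N = 345, and 50.0% of the 228.1 null deaths if 10% of the 345 are lost. The first departs from the stated null base, and the second falls at 28.8 months rather than 26.

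**4. Which fraction does 0.008 indicate?** The one-sided Lan-DeMets O'Brien-Fleming function is α*(t) = 2 − 2Φ(1.960/√t).

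| Fraction | Lan-DeMets interim / final | Classical O'Brien-Fleming interim / final |
|---|---|---|
| 40% | 0.0019 / 0.0494 | 0.0043 / 0.0483 |
| 50% | 0.0056 / 0.0482 | 0.0088 / 0.0467 |

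The stated 0.008 is nearer the 50% row under either boundary. The Lan-DeMets function reaches 0.008 only at a fraction of about 0.55. The stated 0.042 is 0.05 − 0.008 and appears nowhere in the table.

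**5. Does the stated pair control type I error?** With correlation √t between the interim and final statistics, levels of 0.008 and 0.042 give an overall one-sided error of 0.0460 at 40% and 0.0451 at 50%. Both are below 0.05.

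**6. Chance of stopping early under the alternative.** Φ(|ln HR| × √(0.24 × D) − z), with |ln HR| = 0.333:

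| Deaths D | Lan-DeMets level for that fraction | Stated level 0.008 |
|---|---|---|
| 112 (40%, N = 380) | 12% | 25% |
| 140 (50%, N = 380) | 27% | 32% |

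**The case against.** The best defence is that the Interim Analysis section is the specific one and can be followed as it stands: it gives a percentage, a count, a time and both levels. On its own null base with N = 380, the 40%, the 114 events and the 26 months agree closely. So a reader who infers that 114 says nothing about the intended fraction goes too far. This part of the defence stands. It does not remove the 50% in Statistical Methods, and it does not explain an interim level nearer a 50% look.

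Three stronger inferences are tempting and should not be drawn.

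- *That the contradiction inflates type I error, or that no boundary can be computed.* The levels are written down and keep the error below 5% at either fraction. A Lan-DeMets function can also be evaluated at whatever fraction is observed.
- *That the look could be placed opportunistically because the trial is open-label.* The article does not say that the trial is open-label, and nothing in it permits choosing the trigger after seeing data.
- *That the design must move to a final target of 232 deaths and drop the null-hypothesis base.* A null-based count is a usable trigger. With N = 380 and the stated follow-up, about 254 deaths are expected under the alternative, so a stop at 232 could shorten the planned minimum follow-up. That would be a design change, not a correction.

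It can also be said that an article may leave the total event count to the full protocol. That is fair for the total alone. It does not excuse two different fractions in the text.

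**Conclusion.** The contradiction is real and concerns a threshold for a decision that may end the trial. Statistical Methods and Interim Analysis disagree on the fraction. The Interim Analysis section also does not fully agree with itself: its count and timing point to 40% at N = 380, while its 0.008 points towards 50%.

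At N = 380 the gap is about 28 deaths and 3.6 months. The chance of an early efficacy stop under the alternative is 12% versus 27% with Lan-DeMets boundaries, or 25% versus 32% at the stated 0.008. Overall one-sided error stays at about 0.045 to 0.046, so error control is not the problem. What is undefined is the timing of the look and the chance of stopping at it.

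These figures assume exponential survival and uniform accrual. The result is not sensitive to the rounding of 56%: with 55% standard-arm survival, 114 is 40.3% of the null total at N = 380 and is reached at 25.1 months. It must be corrected before the interim is run.

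**What to change.** Before the interim analysis, write one information fraction in both Statistical Methods (Phase II, Primary endpoint) and Interim Analysis (Phase II). Beside it, state the interim death count, the total planned deaths, and the N and hypothesis from which they are derived. Replace 0.008 and 0.042 with the levels that the Lan-DeMets O'Brien-Fleming function gives at that fraction: 0.0019 and 0.0494 at 40%, or 0.0056 and 0.0482 at 50% (one-sided 0.05).

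Either fraction is acceptable, and the choice is the sponsor's. On the null base with N = 380 the count would be about 112 deaths at 40% or 140 at 50%.

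The cost is a wording change and a recalculation of two levels, with no change to sample size or follow-up. Choosing 50% puts the look at about 28.8 months rather than the stated 26; choosing 40% leaves it close to the stated time.

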### Secondary endpoints

• Progression-free survival will be analyzed analogously to the primary endpoints. P-value of the logrank test and test within the Cox regression will be interpreted descriptively.

• Safety/Toxicity will be assessed by the type, incidence, severity (graded by the NCT CTCAE Version 4.0), and relatedness of AEs to treatment and by assessment of laboratory parameters related to safety. Tolerability and dosing will be described by numbers of patients in whom treatment was given as planned, delayed or permanently stopped. All analyses will be performed separately for both treatment groups.

A detailed SAP will be designed after initiating the study and before start of data analysis by the biometric center. It will consider all analyses necessary to characterize the study populations and to evaluate the primary and secondary endpoints.

### Interim Analysis

#### Phase I

Besides the planned analysis during and after phase I part, no further interim analysis are planned.

#### Phase II

For the primary aim and the primary endpoint of the phase II, one interim analysis will be performed when 40% of the expected events under the null-hypothesis have occurred. Under the study hypotheses, 114 events will be occurred under the null hypothesis approximately after 26 months after start of recruitment.

Using O'Brien-Fleming approach with one scheduled interim analysis, hypothesis testing would be conducted at an interim significance level of α = 0.008. If significance is found in favour of the test treatment, the study may be stopped with sufficient statistical evidence of efficacy. If the level of significance is not reached at the interim analysis, the study continues to normal completion at which time the hypothesis testing is conducted at a significance level of α = 0.042. This stagewise procedure will have an overall significance of α = 0.05.

If for any reason no confirmative interim analysis will be performed, the final significance level will be 5%.

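### The interim and final test levels of 0.008 and 0.042 do not follow from the named O'Brien-Fleming spending rule and do not give an overall level of 5%

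*Protocol article*

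**What the plan says.** Two places in the protocol article define the phase II decision rule for overall survival.

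- **Statistical Methods, Phase II, Primary endpoint.** The endpoint is to be "analysed by a one sided logrank test of stratified by histology", with alpha of 5%. On the sequential design: "a sequential plan with alpha-spending of De-Mets and Lan with limits of O'Brien and Fleming is applied". On timing: "One interim analysis is planned when 50% of the number of expected events under the null-hypothesis have occurred".
- **Interim Analysis, Phase II.** The look is now at 40% of the expected null-hypothesis events, given as 114 events at about 26 months. An O'Brien-Fleming approach is named again, and "hypothesis testing would be conducted at an interim significance level of α = 0.008". If the trial continues, there is a final analysis "at which time the hypothesis testing is conducted at a significance level of α = 0.042". The section concludes: "This stagewise procedure will have an overall significance of α = 0.05".

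**The concern.** Once the spending function, the overall level, the sidedness and the information fraction are fixed, the two test levels follow by calculation. Here 0.008 and 0.042 sum to exactly 0.050. That is what subtracting the interim level from 5% would produce, and it is not how an O'Brien-Fleming boundary is obtained. The two looks share data, so the final level after a small interim spend should lie close to 5%.

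These are the success criteria for the primary endpoint, and as written the article holds two rules that can disagree. At a 40% look, an interim p-value of 0.004 would meet the printed level but fail the spending function. A final p-value of 0.045 would fail the printed level but meet the spending function.

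**Working it through.** **Inputs from the article.** One-sided alpha 0.05; Lan-DeMets spending of O'Brien-Fleming type; one interim look at information fraction t = 0.40 or t = 0.50; levels 0.008 and 0.042. From Sample Size Calculation, Phase II: 12-month survival 56% against 66%, allocation 2:3, 36 months of accrual plus at least 12 months of follow-up, 138 + 207 = 345 patients before the 10% allowance.

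**Is the design one-sided?** With exponential survival, HR = ln(0.66)/ln(0.56) = 0.717. Schoenfeld's formula with 40:60 allocation then needs 233 events and about 349 patients one-sided, or about 442 two-sided. The stated 345 agrees with one-sided 5%.

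**Step 1: levels under the named rule.** The alpha spent by the interim is α(t) = 2[1 − Φ(1.96/√t)].

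- t = 0.4: 1.96/√0.4 = 3.099, so α = 0.0019.
- t = 0.5: 1.96/√0.5 = 2.772, so α = 0.0056.

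The final limit c solves P(Z₁ > z₁ or Z₂ > c) = 0.05, where Z₁ and Z₂ are bivariate normal with correlation √t and z₁ is the interim limit.

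- t = 0.4: z₁ = 2.887, c = 1.651, final level 0.0494.
- t = 0.5: z₁ = 2.538, c = 1.662, final level 0.0482.

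**Step 2: could another variant give the printed pair?**

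| Rule | 40% look | 50% look |
|---|---|---|
| Lan-DeMets O'Brien-Fleming, one-sided 5% | 0.0019 / 0.0494 | 0.0056 / 0.0482 |
| Lan-DeMets O'Brien-Fleming, two-sided 5% | 0.0008 / 0.0497 | 0.0031 / 0.0490 |
| Classical O'Brien-Fleming, one-sided 5% | 0.0043 / 0.0483 | 0.0088 / 0.0467 |
| Classical O'Brien-Fleming, two-sided 5% | 0.0019 / 0.0492 | 0.0052 / 0.0480 |
| Printed | 0.008 / 0.042 | 0.008 / 0.042 |

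None does. The one-sided spending function reaches 0.008 only at t of about 0.546, which is neither stated timing.

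**Step 3: true overall level of the printed pair.** The limits are z = 2.409 and 1.728. The overall error is 0.008 + 0.042 minus the null probability of crossing both limits.

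- t = 0.4: 0.050 − 0.0040 = 0.0460.
- t = 0.5: 0.050 − 0.0049 = 0.0451.

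Two-sided, the figures are 0.0467 and 0.0458. If 0.008 were kept, the final level giving exactly 5% would be 0.0462 (t = 0.4) or 0.0471 (t = 0.5), still not 0.042.

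**Step 4: consequences.** The article does not give a total event count, so I assume exponential survival and uniform accrual. The probabilities of death by the final analysis are 0.735 (standard) and 0.623 (experimental), so events = 138 × 0.735 + 207 × 0.623 ≈ 230. The expected final Z is √(0.24 × 230) × 0.333 ≈ 2.48, where 0.24 = 0.4 × 0.6 and 0.333 = −ln(0.717).

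| | Printed levels | Named rule |
|---|---|---|
| Early efficacy stop, 40% look (92 events) | 20% | 9% |
| Early efficacy stop, 50% look (115 events) | 26% | 22% |
| Overall power, 40% look | 77.8% | 79.6% |
| Overall power, 50% look | 77.7% | 79.5% |

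The observed HR at a limit is exp(−z/√(0.24 d)) for d events. At d = 114, a level of 0.008 corresponds to HR 0.63, 0.0056 to HR 0.62, and 0.0019 to HR 0.58. Which spending limit belongs to 114 events depends on the total: 114 is about 41% of the 279 null-hypothesis events expected for N = 380, 45% of the 253 for N = 345, and 50% of the 230 expected under the alternative for N = 345.

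**The case against.** The strongest reply is that little harm follows. The printed pair is a conservative split: overall error stays below 5%, so 0.05 holds as an upper bound. The power loss is under 2 percentage points, and it is computed for an unstratified test, whereas the article expects stratification by histology to add power. Crossing the interim limit permits stopping but does not compel it, and a detailed SAP is announced before data analysis. Classical one-sided O'Brien-Fleming gives 0.0088 at 50%, so 0.008 is not far from a recognised bound if the look falls near half the events. The size of the interim discrepancy also depends on the scenario. The contrast of 20% against 9% belongs to a look at 92 of 230 events; at 114 of 230 it narrows to about 25% against 21%.

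Most of this stands as a limit on the size of the problem. It does not rescue the numbers. The article names Lan-DeMets spending, not the classical bound, and no variant tried gives a final level of 0.042. The levels are printed as operative thresholds beside a rule that contradicts them, so this is not detail left to the SAP.

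**Conclusion.** The printed levels are wrong as written. They do not follow from the named rule at either stated timing, and the overall level is 0.0460 or 0.0451, not 0.05. These results need only the stated alpha, sidedness and information fraction.

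The error is conservative overall. Its practical effects are an interim limit 1.4 times (50%) to 4 times (40%) looser than the spending function allows, a final test stricter than necessary, and a power loss of just under 2 points. The power and early-stopping figures also rest on exponential survival, about 230 events and an unstratified test.

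**What to change.** Delete 0.008 and 0.042 from Interim Analysis, Phase II. State that both limits are computed from the one-sided 5% Lan-DeMets O'Brien-Fleming function at the information fraction observed at the look, and name the target number of events that defines 100%. Reconcile the 40% and 50% timings between the two sections and print the matching planned levels: 0.0019 and 0.0494 for 40%, or 0.0056 and 0.0482 for 50%.

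The cost is two numbers and a sentence or two, with no change to the sample size. The interim limit becomes harder to cross and the final test easier. Make the change before any unblinded interim result is seen, because choosing between limits afterwards would compromise the confirmatory test.

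### The only phase II interim rule has no branch for survival clearly worse on carbon; a non-binding lower limit at the same look would cost almost nothing

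*Protocol article*

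**What the plan says.** The primary survival endpoint "was planned to be analysed by a one sided logrank test of stratified by histology", with an alternative only in the direction of better survival on carbon (Statistical Methods, Phase II, Primary endpoint). One interim look is planned. The Interim Analysis section (Phase II) places it at 114 deaths, about 26 months after recruitment starts, and gives it two outcomes:

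- Level of 0.008 reached: "If significance is found in favour of the test treatment, the study may be stopped with sufficient statistical evidence of efficacy".
- Level not reached: "If the level of significance is not reached at the interim analysis, the study continues to normal completion", with a final test at 0.042.

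The Sample Size Calculation (Phase II) sets recruitment at 36 months and states that "an unbalanced randomization allocation ratio of 2:3 was chosen", so 60% of patients go to carbon. Phase II toxicity is described by arm, with no stopping criterion (Secondary endpoints). The rule based on dose-limiting toxicity (Dose Escalation Scheme) governs phase I only.

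**The concern.** The two branches are meant to cover every interim result. With a one-sided test, the second branch holds a small benefit, no difference and a marked excess of deaths on carbon alike. The written rule treats all three the same way, at a time when recruitment is still open and three in five of the remaining patients would be allocated to carbon. If the 0.008 were read as two-sided, significance against carbon would still have no stated action. At stake is whether the one planned comparison of survival during recruitment can prompt a review if the experimental arm is doing worse.

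**Working it through.** **Inputs from the protocol article.** 12-month survival 56% (standard) and 66% (carbon); one-sided α = 0.05; power 80%; allocation 2:3; 36 months' accrual and at least 12 months' follow-up; N = 345, or 380 with the 10% allowance; 114 interim deaths.

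**Assumptions.** Exponential survival, proportional hazards and uniform accrual. Positive Z favours carbon.

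**Reproducing the plan's figures**

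- Design hazard ratio (HR) = ln 0.66 / ln 0.56 = 0.717.
- Deaths needed = (1.645 + 0.842)² / (0.4 × 0.6 × (ln 0.717)²) = 232.04, rounded up to 233.
- Probability of death by the end of the study: 0.735 (standard) and 0.623 (carbon); weighted 0.4 × 0.735 + 0.6 × 0.623 = 0.667.
- N = 233 / 0.667 ≈ 349, against 345 stated. A two-sided 5% test would need about 442, so the stated size is one-sided.
- Final deaths under the design effect: 345 × 0.667 ≈ 230.
- Interim deaths: 0.40 × 380 × 0.735 ≈ 112, against 114 stated.

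**What the written rule does.** At 114 deaths the information is 114 × 0.24 = 27.36. Its square root is 5.231, so SE(log HR) = 1/5.231 = 0.191. The one-sided 0.008 level needs an observed HR of about exp(-2.409 × 0.191) = 0.63 or lower. The probability of reaching it is 25% at HR 0.717, 0.8% at HR 1.0, 0.04% at HR 1.2 and about 0.002% at HR 1.4. If carbon is worse, the trial is in the continue branch almost always.

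**Patients still to be randomised.** At month 26, 10/36 of accrual remains: 345 × 10/36 ≈ 96 to 380 × 10/36 ≈ 106. If carbon is worse, 114 deaths arrive sooner. For a true HR of 1.2 to 1.4 the remainder is about 97 to 106 (N = 345) or 123 to 132 (N = 380). Overall that is roughly 95 to 130, of whom 60%, about 57 to 78, would go to carbon. At HR 1.4 the 12-month survival on carbon would be 0.56^1.4 ≈ 44%, against 56%.

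**What a lower limit would do.** Take Z ≤ -1.645, that is, an observed HR of exp(1.645 × 0.191) ≈ 1.37 or worse. The probability of crossing is Φ(-1.645 + 5.231 × ln HR):

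| True HR | 5.231 × ln HR | P(cross) |
|---|---|---|
| 0.717 | -1.743 | 0.04% |
| 0.9 | -0.551 | 1.4% |
| 1.0 | 0 | 5.0% |
| 1.2 | 0.954 | 24% |
| 1.4 | 1.760 | 55% |
| 1.5 | 2.121 | 68% |

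**Power at HR 0.717.** Bivariate normal, correlation √(114/230). With O'Brien-Fleming spending levels at about half the information (0.0056/0.0482), power is 79.41% without the limit and 79.41% with it. With the plan's own 0.008/0.042 it is 77.69% both ways.

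**Type I error.** Stopping for a low Z can only remove rejections in favour of carbon, so it cannot raise the one-sided error. If the limit is non-binding, the efficacy levels stay as they are.

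**The case against.** The strongest reply is that the sentence on continuing is mainly an alpha rule. It goes on to give the final level and the overall 5%, which is usual wording for an efficacy-only group-sequential design. Such a design is legitimate. Stopping for harm is commonly handled in the full protocol or by a monitoring body, and neither is shown. This stands to the following extent: a reader might infer that the plan requires randomisation to go on during an excess of deaths whatever a monitoring body advises. The article does not say that, and nothing in it forbids such a stop. The absence of a monitoring body from an article is no finding. What remains is that the article writes out both branches with their actions, that the second covers results clearly against carbon, and that no other phase II section qualifies it.

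Two further readings are tempting and unsupported. The Discussion says that no patient with recurrent glioma has been treated with carbon ions, but that describes the position before the trial. By phase II, up to 56 such patients (7 levels × 8) will have been treated in phase I. They are not randomised, so comparative survival is still untested, but the regimen is not new to this population.

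A reader might also prefer a limit at Z ≤ -1.0, which catches more harmful cases: 78% at HR 1.4. But it corresponds to an observed HR of only about 1.21 and is crossed in 16% of trials at HR 1.0 and 6% at HR 0.9. That is a futility bound, not evidence of clearly worse survival.

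**Conclusion.** The point holds as a design improvement. The written interim rule has no branch for clearly inferior survival on carbon, and the look falls while roughly 95 to 130 patients are still to be randomised. A non-binding limit at Z ≤ -1.645 would flag 55% of trials at a true HR of 1.4 and 68% at 1.5. The price is a 5% chance of a review when the arms are equal and 1.4% at HR 0.9.

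These figures assume exponential survival, proportional hazards, uniform accrual, 114 interim deaths and about 230 final deaths. The Statistical Methods section puts the look at 50% of expected events where the Interim Analysis section says 40%; the crossing probabilities use the stated count of 114 deaths and would shift with a different count. A reader might infer that the primary test is invalid. It is not: type I error and power are not at issue here.

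**What to change.** In the Interim Analysis section (Phase II), and in the SAP, replace the two-way rule with a three-way rule:

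1. Efficacy limit reached: as planned.
2. Limit for inferior survival reached, on the same stratified log-rank statistic at the same look (for example Z ≤ -1.645 against carbon, observed HR about 1.37 or worse at 114 deaths): the randomised comparison is reviewed for stopping.
3. Otherwise: continue to the final analysis.

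State that the lower limit is non-binding, so the efficacy levels and type I error are unchanged. The value -1.645 is an example; the sponsor should choose the limit with the crossing probabilities in view. The change takes a few lines of text and needs no extra look, data or patients. Its statistical cost is the 5% chance of a review at HR 1.0 and 1.4% at HR 0.9.
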